### Randomization

Randomization will be computer-generated in randomized blocks using the randomization.com system. The process will be carried out by a volunteer not affiliated with the research, who will preserve allocation anonymity, randomly separating the individuals into a control group (CG) and experimental group (EG). The volunteer will also prepare sealed envelopes, using codes to represent the groups.

Only the researchers in charge of conducting the training sessions will be aware of meaning of each code and participant allocation. They will open the envelope corresponding to the patient number before patients start the training.

The researchers responsible for the initial assessment and reassessment will not be informed of allocation during data collection and statistical analysis. Data analysis will also be performed by one of the evaluators, who will only have access to the codification and will not be informed about which group each code corresponds to.

The present protocol has been prepared in accordance with relevant items from the SPIRIT Checklist (see Additional file 1) and the SPIRIT Figure (Fig. 1).

### Intervention

This protocol will be based on those of El-Whishy [18] and Santiago [19]. Training will start on the day following the initial assessment, which will be divided into 2 days.

The subjects who are randomly allocated to the EG will be submitted to a protocol consisting of five training stages, as follows: awareness, problem identification, progressive relaxation, MI of the task and PP of the task. The CG will undergo the following stages: awareness, problem explanation, progressive relaxation and PP of the task; that is, stages 1, 2, 3 and 5.

After opening the identification envelope, the researcher in charge of training will describe the stages that the participants will be submitted to. Before this, blood pressure and heart rate will be measured and monitored by a digital sphygmomanometer (Visomat Comfort III, Incoterm*®,* São Paulo, Brazil).

In the event that patients exhibit altered vital signs, they will be asked to remain seated and try to relax. If the situation persists, the patient will be instructed to visit their physician.

Before training sessions begin, the researcher in charge will ask the patient to walk around the course to be used that day if it is the first, fifth or ninth session, so that the execution time can be recorded and used during the fourth stage. A detailed description of the training protocol is shown below.

### EG and CG protocol

#### Awareness

In the EG, the subjects will analyze the sequence of the gait cycle, in order to understand the gait phases, which should facilitate motor planning and problem identification. The therapist will show a video of a typical normal gait for an adult man or woman with no pathologies and will compare it to the video of the patient’s own gait. The patient will watch the videos in two planes: the coronal and sagittal, which will be shown more than once. After viewing both videos, the patient will be encouraged to analyze and score their own gait characteristics, which differ from those of the individuals with no pathology. If the subject cannot adequately verbalize, the therapist can give hints on which important aspects should be observed. The CG subjects will watch a video on PD that does not mention physical therapy treatments for gait. The time allotted to watch the video will be the same as for the EG.

#### Problem identification/explanation

In the EG, the subjects will identify gait problems and compare their walking and typical gait. Next, they will use comparative information for feedback. It may be necessary to encourage the patient in terms of the characteristics that should be compared, such as arm balance, stride length and gait speed. In the CG, the patients will explain their understanding of the video that they watched in the previous stage.

#### Progressive relaxation

At the start, both groups’ participants will be instructed to sit comfortably in a chair with their backs supported, hands in their lap, close their eyes while breathing slowly and deeply through the nose and say the word “hoo” silently to themselves while exhaling. They will be instructed to concentrate and be aware of their breathing, while repeating the respiratory pattern 10 times.

#### MI of gait

In the first part, the EG subjects will be asked to mentally repeat from stage 1 to the problem-identification stage, with their eyes closed. After the mental-imagery phase, subjects will be asked to verbalize a difference between normal gait sequences and their own gait. In the second part, they will practice MI of the sequence of movements of the gait pattern in adults with no pathologies (considered the typical pattern), imagining themselves walking along a straight course and feeling all the components of gait (for example, movement, muscle action, arm balance and weight bearing), while correcting the problems found in the video. Seated and with their eyes closed, they will imagine each movement stage in the kinesthetic modality, where “feeling” must be emphasized: the movement, muscle action, arm balance, weight-bearing, etc.

During the EG stage, the setting should be as quiet as possible and the patient will be asked to wear noise-canceling earphones. There will be three sessions of 10 repetitions. Each repetition will be controlled and last the same amount of time as that measured during the patient’s lap around the course, with 20 s rest between each repetition. At each repetition, patients will be instructed to close their eyes and imagine the sensation present while rising from a chair, adopting their posture and when walking around the course. They must remember to start with the least affected limb in order to perform the gait pattern, making the expected corrections. At the end of each repetition, the patient will receive a sign from the therapist, who will provide instructions and time the duration of the next repetition.

Each MI session will be held alternately with the PP sessions (described in the next topic: “stage 5 PP of gait”). MI will always be prior to the PP of gait.

#### PP of gait

Both groups will engage in the PP of gait, paying close attention to the sequence. This will be performed on a flat, firm, 6-m-long surface, following the same number of series and repetitions as in the second part of MI. In the EG, the second part of MI and PP will be repeated alternately. In the CG, execution will occur normally, without alternate repetitions of stages 4 and 5, but there will also be guidelines on the PP stages to be performed.

In the first of 12 sessions, during stage 5, the patient will be asked to walk around the course as best they can. During the repetitions, the researcher can verbalize a number of feedback sentences, in relation to the aspects of gait that should receive attention and be corrected. This will be allowed until the second session. From the third session onwards, at the onset of PP, patients will be reminded about the corrections previously highlighted.

From the fifth session onwards, EG subjects will undergo the previously described protocol; however, in stage 4, the imagined gait will be in a setting with obstacles, represented by a busy street. The patient will be instructed to imagine walking along the street, dodging people, avoiding holes, walking down sidewalks and entering stores with narrow doorways. In stage 5, they will perform gait with obstacles, as follows: zigzagging around two cones, walking through a narrow doorway, climbing up and down one step, climbing up and down one ramp, climbing up and down one step, stepping over three mini barriers and one small box, climbing up and down one small ladder, walking over foam and then returning over the entire course.

In the first repetition of the fifth session in the PP portion, the obstacles will be arranged in the same way as shown in the videos, and the patient will start at the beginning of the circuit. At each series conducted, the point where the patient starts the trajectory will be changed and this pattern will be used for the others. In the subsequent sessions, the course will be slightly changed and based on photographs and the same change will be repeated with all the patients. The CG will also perform the aforementioned protocol, but in stage 5, gait will be executed in an environment with obstacles (the same as the EG).

From the ninth training session onwards, EG subjects will carry out both MI and PP of gait with two tasks. Mental imagery will involve a supermarket, where the patient will be instructed to imagine walking around the environment, shopping for products beginning with a letter that will be drawn at each series.

The dual task performed in stage 5 will be different at each session, progressing in difficulty. In the ninth session, the patient must say words starting with the letters drawn in each series; in the 10th session, they will be asked the names of fruits according to the letters selected; in the 11th session, it will be the names of animals and, finally, in the 12th session they will perform subtractions, starting with a decreasing sequence of 90 minus 3. Furthermore, another motor activity will be associated with gait such as picking up an object along the way and bringing it back to the start of the course. In the CG, subjects will only engage in dual-task gait, following the same protocol of activities established for the EG.

This protocol will be applied on the day following initial assessment, executed in 12 training sessions of at most 90 min, three times a week for 4 weeks. Experimental group individuals will be instructed to continue to practice MI of gait in their daily lives during the training period. They will be instructed to fill in a diary with information on the quantity of days, number of repetitions and duration of the training performed at home. All the participants will be reassessed 1, 7 and 30 days after the last training session in terms of the kinematic variables of gait using the Qualisys Motion Capture System®, mobility using the TUG and EEG activity via Emotiv EPOC+. During the gait test, the patient will be instructed to walk as they did over the past days, since the beginning of the study participation. As the evaluator is blind to allocation groups, they will not know whether the patient is making corrections or not in the gait. The schematic study design is shown in Fig. 2.

**Fig. 2 Fig2:**
[figure not shown]
The schematic study design

### Data analysis

Data analysis will be conducted with the following variables: (1) Kinematic: speed (m/s), stride length (m), stance and swing time (s) of the most affected limb, hip range of motion, maximum hip extension during stance (°), maximum hip flexion during swing (°), maximum knee flexion during swing (°) and ankle dorsiflexion (°); (2) EEG activity: alpha (8–12 Hz)- and beta (13–30 Hz)-frequency bands; and (3) Mobility: average time to conduct the TUG.

Analysis of variance with repeated measures will be used to determine whether there are statistically significant differences between baseline, post training and monitoring measures of the CG and the EG.

Group descriptions will be presented as means and standard deviations. Intention-to-treat analysis will be conducted for dropout data, using the last available value to represent the absent assessment sessions.

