### Sample size estimates

The sample size was calculated using the OpenEpi public domain program, version 3.01 [21]. The calculation, based on the outcome variable “hip range of motion” of individuals with PD submitted to MI associated with the PP of gait, obtained by El-Whishy et al. [18] A power of 80% was considered as well as a 95% confidence interval. The mean and standard deviations were 54.7° and 7.2°, respectively, from which the sample size of 34 individuals (17 in each group) was obtained. Added to this value was 10% for possible sample losses, resulting in a final sample of 40 individuals, 20 each in the two groups under study.

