### Outcomes

#### Primary outcome

The hip range of motion, a kinematic variable of gait, will be obtained by the Qualisys Motion Capture System (Qualisys Medical AB, 411 13, Gothenburg, Sweden). This system records the spatio-temporal variables of gait, as well as the angular variations of the hip, knee and ankle joints. It is a photographic system based on a video that reconstructs movement in three dimensions (3D), composed of six Qualisys Oqus 300 cameras, connected in series and that emit and capture infrared light, which is reflected by spherical markers placed on specific anatomical structures.

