#### Secondary outcomes

The secondary outcomes will be the spectral power of the alpha and beta rhythms, intra- and inter-hemisphere coherence between frontal and fronto-central channels and mobility. Electroencephalographic activity will be measured by Emotiv EPOC+, which provides EEG data. The device uses contact sensors attached to the flexible plastic arms of a wireless headset. The headset has 14 sensors that are able to detect facial expressions, head rotation, emotions and conscious mental commands. For the present study, the changes in EEG activity captured on the surface of the patient’s head will be monitored before and after 12 training sessions (including follow-ups). MATLAB software will be used to process the data [26, 27]. Mobility will be assessed by the Timed Up and Go Test (TUG). This consists of rising from an ordinary chair (with no arms), walking 3 m, turning through 180°, and sitting down again as fast as possible wearing typical walking shoes. The shorter the time to perform the activity, the better the mobility [28]. The time spent on the two attempts will be recorded using a digital stopwatch.

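### Hip range of motion is the sole primary outcome, but the plan does not say which ANOVA effect or which visit decides it

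*Protocol article*

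**What the plan says.** - **Primary outcome.** One variable stands under this heading: "The hip range of motion, a kinematic variable of gait, will be obtained" by motion capture. No visit and no comparison is attached to it.
- **Secondary outcomes.** "The secondary outcomes will be the spectral power of the alpha and beta rhythms", together with coherence and mobility. No kinematic variable is listed here.
- **Sample size estimates.** The calculation uses hip range of motion with mean 54.7° and SD 7.2°, and gives 17 per group. The error rates are given as: "A power of 80% was considered as well as a 95% confidence interval". The Discussion adds that the trial was sized for differences between the groups in the primary outcome.
- **PP of gait.** "All the participants will be reassessed 1, 7 and 30 days after the last training session". With baseline, that makes four occasions.
- **Data analysis.** The section opens: "Data analysis will be conducted with the following variables: (1) Kinematic: speed (m/s), stride length (m), stance and swing time (s) of the most affected". Its list then goes on to hip range of motion, hip extension, hip flexion, knee flexion and ankle dorsiflexion. The method is: "Analysis of variance with repeated measures will be used to determine whether there are statistically significant differences between baseline, post training and monitoring measures", for both groups.

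**The concern.** A primary outcome is settled only when the variable, the time point and the comparison are all fixed. Here only the variable is. A repeated-measures ANOVA of two groups over four occasions usually reports a group effect, a time effect and a group-by-time interaction, and it is often followed by comparisons at single visits. The planned wording fits more than one of these.

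The visit labels do not settle it either. The Design section places weeks 5 and 6 together as the end of the intervention, so *post training* could mean day 1, day 7 or both.

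Two things are at stake. If the deciding test can be picked after the data are seen, the 5% error rate no longer holds for the primary claim. The candidates also answer different questions: the group main effect averages in the pre-training baseline, where no training effect can exist.

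In addition, eight kinematic variables go through the same ANOVA without being primary or secondary. A reader of the results could not tell what weight to give them.

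**Working it through.** **1. What the sample size implies.** The 17 per group cannot be reproduced forwards, because only one mean (54.7°) and one SD (7.2°) are given and no difference. Solving backwards, with 95% confidence read as two-sided 5% and power 80%:

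d = (1.960 + 0.842) × √(2/17) = 0.961, and 0.961 × 7.2° = 6.9°.

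With the t distribution the result is 7.1° (d about 0.99). So 17 per group fits one two-group comparison of about 7°. The Data analysis section does not identify that comparison.

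**2. Number of kinematic variables.** Speed, stride length, stance time, swing time, hip range of motion, hip extension, hip flexion, knee flexion and ankle dorsiflexion make nine. One is primary, so eight have no tier.

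**3. Error rate for hip range of motion alone, by hand.**
- Group or interaction, treated as independent: 1 − 0.95² = 9.75%.
- Any of three visits: 1 − 0.95³ = 14.3% if independent. Whatever the correlation, it cannot exceed 3 × 5% = 15%.

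**4. The same by simulation.** Settings: no true effect, 20 per group, four occasions, no missing data, each test at two-sided 5%. The document gives no correlations, so they are assumed. They were either equal across all occasions (0.5, 0.7 or 0.9), or 0.5–0.7 between baseline and later visits with 0.7–0.9 among later visits.

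| What may carry the claim | Equal correlations | Unequal correlations |
|---|---|---|
| One interaction test, named in advance | 4.6–5.5% | 5.4–8.1% without sphericity correction |
| Baseline-adjusted difference at day 1 | about 5% | about 5% |
| Group or interaction | 9–10% | 10–13% |
| Any of three visits (raw, change or baseline-adjusted) | 8–14% | 8–12% |
| Group, interaction or any visit-wise change | 17–19% | 14–16% |

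The lowest figures, just over 8%, arise when visits are very highly correlated.

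**5. Dilution in the group main effect.** Suppose the effect is d = 0.97 at all three later visits and zero at baseline. The group main effect then estimates (0 + 3 × 0.97)/4 = 0.73. Simulated with 17 per group, its power is about 57–74%, and it would be lower if the effect fades. The baseline-adjusted day-1 difference has about 87–96% power when baseline and day 1 correlate at 0.5–0.7. The interaction test has 82% or more under the same sustained effect.

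**The case against.** The strongest reply is that the protocol does rank its outcomes. Hip range of motion is alone under the primary heading and the sample size rests on it. The Data analysis section is a short list of what will be analysed and does not cancel that ranking. Comparing groups over baseline and later measures points most naturally to the interaction. If that single test decides, the error rate is about 5%. Separate claims from group and interaction tests are an inference from usual ANOVA output and are not written in the protocol. Post-hoc contrasts, sphericity correction and multiplicity rules are also ordinary content of an analysis plan that is not shown here.

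Much of this stands, and it limits the point. Three stronger readings should not be drawn:
- **All nine gait variables rank equally.** A reader might infer this and compute 1 − 0.95⁹ = 37% for the claim that motor imagery improves gait. The Primary outcome section contradicts the premise, and no rule lets any significant gait variable count as success.
- **The error rate is inflated as written.** It is inflated only if the choice is left open until the data are seen.
- **The SD of 7.2° must be a post-training value because the source study had no follow-up.** Lack of follow-up does not exclude a baseline SD, and the article does not say when it was measured.

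What does not fall away is the open definition. The time point of a primary outcome belongs to the outcome itself, and the article sets out variables, method and missing-data rule while leaving the deciding comparison ambiguous.

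**Conclusion.** The point holds in a limited form. Hip range of motion is clearly the primary outcome, but neither the effect nor the visit that decides it is fixed, although the trial was sized on one comparison between the groups. A free choice between the group and interaction tests, or among the three visits, puts the error rate for this one variable at about 9–15% instead of 5%, and at up to about 19% if all routes are open. A single interaction test named in advance would keep it near 5%.

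These figures assume the stated correlations, complete data and two-sided 5% tests. That the eight other kinematic variables belong to no outcome tier follows from the text and needs no assumption. This should be corrected, and the correction needs no new data.

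**What to change.** In the Outcomes and Data analysis sections:
1. Name one confirmatory test: the baseline-adjusted difference between experimental and control groups in hip range of motion at one pre-specified visit, two-sided 5%. Day 1 is a reasonable choice because it is the first assessment after training. This matches the single two-group comparison behind the sample size. Naming the interaction test alone, with a sphericity correction, would also control the error rate, but it would not say when or in which direction the groups differ.
2. Report days 7 and 30 as retention. If claims are wanted there, test day 7 and then day 30 in fixed sequence after a significant day-1 result.
3. Label the other eight kinematic variables exploratory, reported with confidence intervals. Holm adjustment across the named secondary outcomes is optional.

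The cost is a few sentences, with no change to visits, measurements or sample size. The small downside is that fewer variables and visits can support a headline claim.

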## Discussion

The protocol aims to determine the effects of motor-imagery training on gait and the EEG activity of individuals with PD. This protocol was based on those of Santiago [19] and El-Whishy [18], but the type of observation, follow-up and training time were altered.

In Santiago’s protocol [19], the action was visualized using images of the sequential stages of gait. It is a static method that does not resemble the real pattern. The protocol, based on El-Whishy [18], involves observing the action using videos of normal gait and of a patient with PD, enabling better identification of gait changes and familiarizing individuals with their daily gait pattern, making the training more dynamic.

The second alteration is related to the lack of follow-up in El-Whishy’s protocol [18]. It is known that the presence of a follow-up is important in confirming the retention time of the observed effects. This protocol, which is different from the aforementioned, suggests a follow-up in order for these effects can be assessed.

The third and last alteration is related to the training used. Based on the study by Santiago [19] and El-Whishy’s protocol [18], it is suggested that patients with PD require more time to achieve favorable results. As such, this study proposed to use a longer training period in order to investigate whether the increase in MI training associated with PP is able to produce benefits superior to those of PP alone.

The methodological strength of the proposed protocol lies in the fact that it is a prospectively registered randomized controlled study. The study also includes random allocation and masking, in addition to an intent-to-treat analysis. The sample size was calculated to provide an adequate statistical base to identify intergroup differences in the primary outcome. This study has limitations, given that the participants and therapist cannot be blinded in complex interventions. Moreover, it is difficult to ensure that patients will imagine movement, that they will use this imagination in the kinesthetic modality and in the number of repetitions proposed.

In conclusion, the results of the present study may provide an important advance in neurological rehabilitation. An easy-access, low-cost intervention may help improve gait, EEG activity and mobility in individuals with PD.

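### Baseline hip range of motion is a response level in the repeated-measures ANOVA, the deciding term is not named, and the stated 80% power belongs to neither candidate test

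*Protocol article*

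**What the plan says.** The Data analysis section gives one method for all outcomes: "Analysis of variance with repeated measures will be used to determine whether there are statistically significant differences between baseline, post training and monitoring measures", for the control group (CG) and the experimental group (EG). It names no baseline covariate and no deciding term. The PP of gait section sets reassessments at 1, 7 and 30 days after the last session, so the time factor has four levels including baseline.

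The Sample size section states: "A power of 80% was considered as well as a 95% confidence interval". Its numerical inputs are these: "The mean and standard deviations were 54.7° and 7.2°, respectively", "from which the sample size of 34 individuals (17 in each group) was obtained". It gives no second mean, no difference and no correlation between visits. After an allowance for losses the target is 20 per group.

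The Discussion then claims: "The sample size was calculated to provide an adequate statistical base to identify intergroup differences in the primary outcome".

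**The concern.** Patients are randomised after the initial assessment, so treatment cannot affect baseline. Making it a response level has a different consequence for each of the two tests that the ANOVA offers.

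- **Group main effect (1 df).** It averages the group difference over four visits, one of which is null by design. A sustained difference shrinks to three quarters of its size.
- **Group-by-time interaction (3 df).** It is not diluted in this way, because baseline supplies its contrast. But it spreads one directional question over three degrees of freedom and gives no single estimate in degrees.

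The Discussion attaches the sample size to a between-group difference, yet neither test is the comparison of two means that one mean, one SD and 17 per group suggest. The wording also leaves room to draw conclusions from change over time within a group, whereas the stated question is whether imagery plus practice is better than practice alone. At stake are precision that the trial already has in hand and a power claim that cannot be matched to the analysis.

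**Working it through.** **Inputs from the protocol.** Power 80%; 95% confidence, read as two-sided alpha 0.05 (sidedness is not stated); SD 7.2°, so variance 51.84; 17 per group, raised to 20; four visits.

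**Assumptions.** The difference delta and the within-patient correlation rho are not given. Rho is taken as equal between all visits, at 0.3, 0.5 and 0.7.

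**The plan's own figure.** 17 per group cannot be reproduced, because no difference is stated. Back-solving with the normal approximation:

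delta = (1.960 + 0.842) × 7.2 × √(2/17) = 6.92°, or 0.96 SD.

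A two-sample t-test at one visit has 77.5% power for 6.92° at 17 per group; it needs 7.14° for 80%. The value 6.92° is used below.

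**Formulas, with n = 17, rho = 0.5 and a sustained effect**

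1. Main effect. Difference 0.75 × 6.92 = 5.19. Variance of a patient's four-visit mean 51.84 × (1 + 3 × 0.5)/4 = 32.4. SE = √(2 × 32.4/17) = 1.95. Noncentrality 2.66 on 32 df: power 73%.
2. Interaction. The squared deviations of the profile (0, 1, 1, 1) from its mean sum to 0.75. Noncentrality = (17/2) × 0.75 × 6.92² / (51.84 × 0.5) = 11.8 on 3 and 96 df: power 82%.
3. Day 1, baseline as covariate. Residual variance 51.84 × (1 − 0.5²) = 38.88. With the factor 1 + 1/(2n − 4) = 1.033 for chance baseline imbalance, SE = √(2 × 38.88/17 × 1.033) = 2.17. Noncentrality 3.18 on 31 df: power 87%.
4. Mean of days 1, 7 and 30, baseline as covariate. Residual variance 51.84 × [(1 + 2 × 0.5)/3 − 0.5²] = 21.6. SE = √(2 × 21.6/17 × 1.033) = 1.62. Noncentrality 4.27 on 31 df: power above 98%.

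**Power for a sustained 6.92°**

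| Test | n per group | rho 0.3 | rho 0.5 | rho 0.7 |
|---|---|---|---|---|
| Group main effect | 17 | 84% | 73% | 64% |
| Group-by-time | 17 | 66% | 82% | 97% |
| Day 1, baseline-adjusted | 17 | 80% | 87% | 96% |
| Post-training mean, baseline-adjusted | 17 | 98% | ≥98% | >99% |
| Group main effect | 20 | 90% | 80% | 71% |
| Group-by-time | 20 | 74% | 88% | 99% |

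The main effect falls below 80% when rho exceeds about 0.37 (17 per group) or 0.50 (20 per group). The interaction falls below 80% when rho is under about 0.48 or 0.39. The two tests fail in opposite directions.

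**If the effect fades (n = 17, rho = 0.5)**

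| Effect at days 1, 7, 30 | Main effect | Group-by-time | Day 1 adjusted | Post-training mean adjusted |
|---|---|---|---|---|
| 100%, 75%, 50% | 49% | 67% | 87% | 87% |
| 100%, 50%, 0% | 25% | 78% | 87% | about 55% |

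**The case against.** A repeated-measures ANOVA that includes baseline is common and, under its assumptions, valid in a randomised trial. Lower efficiency is not invalidity. The wording about differences across visits in the two groups points most naturally to the interaction, and that test reaches 80% for a sustained effect once rho is about 0.5. The Discussion wants follow-up in order to judge retention, so the profile over time is a stated interest. A fuller analysis plan, not shown here, may name the deciding term.

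Much of this stands, and it rules out three stronger readings.

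- A reader might infer that one group test suffers both dilution and 3 df. It does not: dilution belongs to the main effect and the 3 df to the interaction.
- A reader might infer that the trial simply falls below 80% power. The documents do not support this, because they give neither the difference nor the correlation, and the answer reverses with rho and with the term tested.
- A reader might infer from the unequal visit spacing that sphericity fails and type I error is inflated. That needs assumed correlations and an uncorrected F-test, and the protocol does not say that the test is uncorrected.

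What the objection does not remove is that the article itself puts baseline among the compared levels and claims power for a between-group difference that this model does not directly estimate.

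**Conclusion.** The point holds in limited form. The plan treats baseline as a response, leaves open which term decides, and attaches its 80% to neither. Under the assumed sustained 6.92° and rho from 0.3 to 0.7, power ranges from 64% to 97% at 17 per group and from 71% to 99% at 20 per group, depending on term and correlation.

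For a sustained effect, the baseline-adjusted post-training mean has at least as much power as either ANOVA test across this range. Adjusted day 1 stays at about 80% or more, but it does not win everywhere: the main effect is ahead at rho 0.3 (84% against 80%), and the interaction is level with it at rho 0.7 (97% against 96%).

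All these figures rest on the back-solved difference, the cited SD, equal correlations and complete data. This is a cheap gain in precision and clarity. It does not show that the planned analysis is invalid.

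**What to change.** State one primary contrast in advance: the EG minus CG difference in hip range of motion, adjusted for baseline hip range of motion, either at one named post-training visit (for example day 1) or as the mean of days 1, 7 and 30. Estimate it from a mixed model of the post-training values with baseline, group, visit and group-by-visit, and report it in degrees with a 95% CI. Report the other visits as secondary evidence on retention. Do not base conclusions on within-group change. State the difference that the sample size assumes, and tie the power to this contrast.

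The cost is analysis wording, since baseline is already measured, and the change should be made before unblinding. There is one real trade-off. If the effect has gone by day 30, the post-training mean is weaker than the planned interaction (about 55% against 78% at rho 0.5, 17 per group), while adjusted day 1 is not (87%). The choice should follow from whether the trial's main question is the immediate effect or the average effect over follow-up.
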